### Randomized Controlled Trial

Randomization will be conducted using an interactive web response system. Participants who meet all inclusion criteria will be assigned to either the experimental group or the control group according to a pregenerated randomization list in the order of enrollment.

The randomization list will be generated using the PROC PLAN procedure in the SAS software (version 18.0.1; SAS Institute). The block size and seed number used for the randomization sequence will be randomly determined by a statistician responsible for randomization at the clinical trial center.

Access to the randomization schedule will be restricted to the designated statistician only. Because allocation will be implemented through a centralized randomization system, the investigators will not have prior knowledge of the randomization sequence or the assignment results, ensuring allocation concealment.

Randomization will be performed after eligibility has been confirmed and the screening procedures have been completed.

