### Design

Using a prospective design, we will collect longitudinal data on patients with SUD for subsequent analysis. Participants will be assigned in a 1:1 randomized fashion to a control group (TAU) or an experimental group (TAU+D-STOP). The trial will be conducted in an open-label manner. The primary aim is to demonstrate the superiority of the experimental arm over the control arm in treatment efficacy. Outcomes will be derived by integrating quantitative and qualitative data sources, including measures captured within the D-STOP app and standardized diagnostic and assessment instruments.

The meaning and implementation of TAU may vary across different medical specialties. In this study, TAU refers to maintaining the medications and treatment approaches that participants were receiving prior to enrollment in the clinical trial. With respect to medications, participants are allowed to reduce the dosage or discontinue previously prescribed medications during the study period; however, increasing the dosage or introducing new medications is not permitted.

Regarding psychosocial treatments, participants engaged in psychosocial intervention programs prior to enrollment (eg, Narcotics Anonymous meetings or 12-step addiction recovery programs) are allowed to continue participating in them. However, the initiation date of the psychosocial treatment program is required to precede the start date of participation in this clinical trial. To minimize potential confounding effects, preference is given to enrolling individuals who are not actively participating in such programs.

In addition, TAU in this study is limited to patients receiving outpatient care only. During the clinical trial period, the total number of hospital visits is scheduled to be 7. If a participant receiving outpatient care requires hospitalization during the trial period, this is considered a relapse-related event and recorded as a notable clinical occurrence; however, such cases are not classified as study withdrawal.

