**Exclusion criteria**
Presence of any advanced, progressive, or unstable disease that could endanger the patientNeurological disorders that may cause cognitive impairmentNeurodegenerative diseases other than depression or severe psychiatric symptoms that would preclude study participationCurrent uncontrolled seizure disorderHistory of brain injury with loss of consciousness lasting more than 1 hour or hospitalization due to traumatic brain injury within the past 3 yearsHearing or visual impairment that would interfere with completion of study requirementsLack of a smartphone capable of installing the investigational medical appPregnant or breastfeeding womenConcurrent participation in another clinical trial or participation in another trial within 30 days prior to screeningDetermination by the investigator to be otherwise unsuitable for the trial

**Table 1. T1:** SPIRIT (Standard Protocol Items: Recommendations for Interventional Trials) checklist: clinical trial–related items.

	Clinical trial period						
	Enrollment—visit 1 (week –4)	Assignment—visit 2 (week 0; baseline)	After assignment				Completion—visit 7 (week 12)
			Visit 3 (week 4)	Visit 4 (week 6)	Visit 5 (week 8)	Visit 6 (week 10)	
Enrollment							
Informed consent	✓						
Screening	✓						
Eligibility check (inclusion and exclusion criteria)	✓						
Demographics and social history	✓						
Physical examination	✓						
Prior medication history	✓						
Pregnancy test	✓	✓	✓^a^	✓^a^	✓^a^	✓^a^	✓^a^
Urine drug test		✓	✓	✓	✓	✓	✓
Randomization		✓					
Intervention							
Investigational DTx^b^		✓	✓	✓	✓	✓	✓
TAU^c^	✓	✓	✓	✓	✓	✓	✓
Assessment							
Abstinence record sheet and mobile record verification							✓
Questionnaire assessment^d^		✓			✓		✓
Compliance and retention assessment		✓	✓	✓	✓	✓	✓
Adverse event monitoring		✓	✓	✓	✓	✓	✓

a Proceed, if applicable.

b DTx: digital therapeutics.

c TAU: treatment as usual.

d Questionnaire assessment: University of Rhode Island Change Assessment Scale–Drug Offender, Hospital Anxiety and Depression Scale, Cognitive Reappraisal Questionnaire, and Behavioral Activation for Depression Scale.

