### Outcome Measures

#### Primary Outcome Measure: Abstinence Success Rate During the Previous 4 Weeks

The primary end point is the abstinence success rate during the final 4 weeks (weeks 9‐12) of the 12-week trial. Abstinence success is defined as meeting both of the following criteria: (1) testing negative on urine drug screens conducted at study visits and (2) reporting “no drug use” on the abstinence check function within D-STOP, consistently maintained throughout the final 4-week period. Participants who satisfy both conditions are classified as achieving abstinence success. The designation of abstinence during the final 4 weeks (weeks 9‐12) of the 12-week trial as the primary efficacy end point was informed by the primary efficacy end point used in the clinical trial of RESET-O.

For the control group, D-STOP is not provided. Instead, abstinence status will be monitored using a paper-based checklist to record participants’ self-reported drug use.

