### Data Collected Within D-STOP

The following variables will be collected: (1) longest abstinence period, (2) total abstinent days, and (3) results from the following psychometric instruments.

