### Data Analysis

All data collected in this trial will be analyzed based on the entire screened population. The number of participants excluded from the safety set and the reasons for exclusion will be reported relative to all enrolled participants. Exclusions from the full analysis set will be described relative to the safety set, and exclusions from the per-protocol set will be described relative to the full analysis set. The primary efficacy analysis will be conducted on the full analysis set according to the intention-to-treat principle.

Participants who discontinue the study prematurely (dropouts) will be included in the analysis in accordance with the intention-to-treat principle. Missing outcome data will not be imputed. If missing values occur in outcomes related to abstinence status, the participant will be considered as having failed (failure) for the purpose of analysis.

For efficacy analyses, the primary end point is the abstinence success rate during the final 4 weeks of the trial. This end point is intended to evaluate the efficacy of the DTx intervention in patients with SUD. Statistical significance will be assessed using multiple logistic regression analyses adjusting for stratification factors such as stimulant vs nonstimulant drug use and baseline abstinence status (abstinent vs nonabstinent) as covariates. The treatment effect will be expressed as the adjusted odds ratio for the experimental group relative to the control group along with 2-sided 95% CIs.

Superiority of the experimental group over the control group will be concluded if both of the following criteria are satisfied: (1) the 2-sided *P* value is less than .05, and (2) the lower bound of the 2-sided 95% CI for the adjusted odds ratio exceeds 1.0.

The secondary efficacy end points include (1) abstinence maintenance rate during the 12-week treatment period, (2) treatment retention rate during the 12-week treatment period, (3) total number of abstinent days, (4) longest duration of consecutive abstinent days, and (5) results from psychiatric and psychological assessment tools.

For these outcomes, multiple logistic regression analyses and analyses of covariance will be performed to compare differences between the experimental and control groups.

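### The questionnaires are listed as collected in an app that only one arm receives, and nothing requires the baseline ones before open-label allocation

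*Protocol article*

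**What the plan says.** - **Condition for allocation** (Randomized Controlled Trial): "Randomization will be performed after eligibility has been confirmed and the screening procedures have been completed". In Table 1 screening and the eligibility check belong to visit 1, so this condition does not cover the questionnaires.
- **Timing** (Table 1): the column headed "Assignment—visit 2 (week 0; baseline") carries the ticks for randomization, the first investigational DTx and the first questionnaire assessment. No order within the visit is given. The questionnaires recur at visit 5 (week 8) and visit 7 (week 12).
- **Blinding** (Design): "The trial will be conducted in an open-label manner".
- **Where the questionnaires are collected** (Data Collected Within D-STOP): the list under this heading includes "results from the following psychometric instruments". The four instruments then described (readiness to change, anxiety and depression, cognitive reappraisal, behavioral activation) are those in the Table 1 footnote.
- **Who has the app** (Primary Outcome Measure): "For the control group, D-STOP is not provided". A paper substitute is described only for the abstinence record. Procedures gives the app at enrollment, and Ethical Considerations gives access after consent; neither limits this to one arm.
- **Analysis** (Data Analysis): for the secondary outcomes, "multiple logistic regression analyses and analyses of covariance will be performed to compare differences between the experimental and control groups". The ANCOVA covariates are not named.

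**The concern.** ANCOVA relies on a baseline covariate that allocation cannot have influenced. All four instruments are self-reports of motivation, mood or coping, which a participant may answer differently on learning that he or she has, or has not, been given the app. If the experimental arm answers in the app, it does so after allocation, and the baseline is then no longer a pre-randomization measurement in that arm. Controls would meanwhile answer in some other way. Both features can separate the arms for reasons unrelated to treatment.

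The exposure is confined to the questionnaire results, the last of the five secondary efficacy end points listed in Data Analysis. The primary end point does not use these scores.

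**Working it through.** **Reading the sections together.** There is no stated figure to reproduce, so the first step is textual.

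1. The heading Data Collected Within D-STOP puts the questionnaires in the app.
2. The primary outcome section withholds the app from controls. Only experimental participants could then answer in the app, and only once allocated. Controls have no stated way to answer.
3. Table 1 puts the first questionnaires at the visit where allocation happens, and the allocation condition does not require them first.
4. Procedures and Ethical Considerations might be read as giving everyone the app before allocation. That contradicts the primary outcome section, and it contradicts Table 1, where the DTx starts at visit 2. Read as applying to the experimental arm only, they put access after allocation again. Neither reading secures a pre-allocation baseline collected alike in both arms.

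**Size if answers shift.** Inputs: 118 participants at 1:1, so 59 per arm (from the document). Assumed, not in the document: outcome SD 1, baseline-outcome correlation rho, recorded experimental-arm baseline shifted by d SD, visit 2 score as ANCOVA covariate.

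Expected bias of the adjusted difference = -rho x d.

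- d = 0.2: -0.3 x 0.2 = -0.06; -0.5 x 0.2 = -0.10; -0.7 x 0.2 = -0.14 SD.
- d = 0.5: -0.15, -0.25 and -0.35 SD for the same three correlations.

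Simulation with no true effect (4,000 trials per setting) reproduces these biases. Two-sided type I error at rho = 0.3, 0.5, 0.7:

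- d = 0: about 0.05 throughout, with no bias.
- d = 0.2: 0.07, 0.09, 0.18.
- d = 0.5: 0.13, 0.33, 0.72.

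With rho = 0.6 and an assumed true effect of 0.4 SD, a shift towards benefit of 0, 0.1, 0.2 or 0.3 SD gives an expected estimate of 0.40, 0.34, 0.28 or 0.22 SD, and power of about 0.77, 0.62, 0.46 or 0.31. With no true effect and a shift of 0.2 or 0.3 SD the other way, false superiority occurs in about 13% or 22% of trials, against a nominal 2.5%.

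**Analysis without the baseline covariate.** In this model the shift touches only the recorded baseline, so a comparison of follow-up scores is unbiased. SE = sqrt(2/59) = 0.184; 0.4/0.184 = 2.17; power = Phi(2.17 - 1.96) = about 0.58. That is below the 0.77 of a clean ANCOVA, but above the 0.46 and 0.31 of an ANCOVA with a baseline shifted by 0.2 or 0.3 SD.

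**The case against.** The strongest reply is that the document never says the baseline follows allocation. Completing the forms first is fully compatible with the randomization sentence, Table 1 groups rows by type rather than by time, and order within a visit is something a journal article commonly leaves to the full protocol. The app reading rests on one heading. Design names app measures and standardized instruments side by side as data sources, and Procedures ties only abstinence status to the app, listing the secondary assessments as a separate visit item. The same heading also covers total abstinent days, which controls must supply without the app. Data Analysis calls baseline abstinence status a stratification factor, so at least that item may be known before allocation. The ANCOVA covariate is unnamed, and the assumed shifts have no source in the document.

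Most of this stands, and it rules out two stronger readings. A reader might infer that experimental-arm baselines *are* taken after allocation and that the comparisons *are* biased. The order is not stated, and bias needs an actual shift in answers. A reader might also infer that the damage could not be repaired. In the model above, an analysis without the baseline covariate is unbiased.

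What the reply does not remove is a conflict in stated text: a two-arm comparison of scores listed as collected in an app that one arm does not have. Nor does any of the passages cited place the four questionnaires before allocation. The stratification remark reaches abstinence status at most.

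**Conclusion.** The point holds as a conflict over how the questionnaires are collected, and as an unprotected baseline. Followed literally, the text permits app-based, post-allocation baselines in the experimental arm and an unstated mode in the control arm. It does not establish that this happens, nor that any result is biased.

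If answers do shift by d SD, the adjusted difference is off by about -rho x d: 0.06 to 0.14 SD in absolute size for d = 0.2 and rho from 0.3 to 0.7, and zero for d = 0. The direction depends on the sign of d, for which the document gives no basis. The figures assume 59 per arm with complete data, and the visit 2 score as covariate, which is usual but not stated. Only the secondary questionnaire end points are exposed. The change is worth making because it is cheap and because later participants can still be protected: 65 of 118 were enrolled by March 6, 2026.

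**What to change.** 1. In Randomized Controlled Trial and in Table 1, state that all visit 2 questionnaires are completed before the interactive web response system is called.
2. State that at every questionnaire visit (weeks 0, 8 and 12) both arms use the same form, outside D-STOP, and move the instruments out from under the heading Data Collected Within D-STOP.
3. Reconcile the primary outcome section, Data Collected Within D-STOP, Procedures, Ethical Considerations and Table 1 on who has the app and from when.
4. For participants already randomized, compare questionnaire and randomization time stamps. If baselines were taken after allocation, add a sensitivity analysis of follow-up scores that keeps all participants and omits the post-allocation baseline covariate. Do not exclude those participants: that selects on a post-randomization feature and could remove much or all of the experimental arm. This analysis does not remove a difference in collection mode at weeks 8 and 12, so item 2 is needed as well.

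The cost is a few sentences, a note to the sites, and one common form in both arms, with no extra visit. The sensitivity analysis costs precision (power about 0.58 rather than 0.77 under the assumptions above) and is needed only if late baselines are found.

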### Participants

This multicenter study is being conducted at 4 medical institutions in South Korea that provide treatment for SUD. Participants will be recruited at university hospitals and general hospitals that include departments of psychiatry using both in-hospital posters and external (community-facing) advertisements.

This study aims to recruit 118 participants across 4 regions in South Korea (Seoul, Daegu, Chuncheon, and Changnyeong) based on estimates from prior research on the required sample size to demonstrate superiority (Textbox 1).

The clinical trial will last 12 weeks, with a total of 7 visits. Each visit window allows for –5 to +5 days from the scheduled date. Participants who fail to attend within this window will be considered to have discontinued the study (Table 1).

Textbox 1.Inclusion and exclusion criteria.

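### Classing any attendance outside ±5 days as study discontinuation can turn a late but abstinent participant into a primary-endpoint failure, and it collides with the hospitalization rule

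*Protocol article*

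**What the plan says.** Protocol article, Participants: seven visits are planned over the 12 weeks, all with the same tolerance: "Each visit window allows for –5 to +5 days from the scheduled date". The article then sets the consequence of missing it: "Participants who fail to attend within this window will be considered to have discontinued the study". It names no exception and does not distinguish early visits from the last one.

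Four other places in the article bear on it:

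- **Primary Outcome Measure.** Success needs negative urine screens taken at study visits as well as self-reported non-use throughout weeks 9-12.
- **Data Analysis.** Missing outcomes are not imputed, and a participant with missing abstinence status counts as a failure. Dropouts stay in the analysis.
- **Design.** A participant who needs hospital admission has a relapse-related event recorded, but "such cases are not classified as study withdrawal".
- **Treatment Retention Rate.** Retention means completing all trial procedures without leaving early.

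Under Procedures, a participant who relapses in weeks 1-8 continues in the trial. Only relapse in weeks 9-12 is a treatment failure.

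**The concern.** Being late for an appointment and leaving a study are different events, and the article gives them the same label. The label matters because the primary endpoint depends on urine tests from later visits and because missing abstinence status is scored as failure. If discontinuation ends data collection, a scheduling slip creates a missing outcome that could have been obtained, and that outcome is then counted against the participant.

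The result is hard to defend on efficacy grounds. Someone who relapses at week 4 but attends on time can still be a primary success. Someone abstinent throughout who attends week 4 six days late could not be. The retention endpoint would also partly measure punctuality. In an open-label trial, any difference between arms in punctuality would pass into both endpoints.

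**Working it through.** **Plan's own figure.** There is none to reproduce. The article gives no expected miss rate, dropout rate or abstinence rates, so every rate below is an assumption.

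**Step 1: the windows.** Table 1 places the five post-baseline visits at weeks 4, 6, 8, 10 and 12. With baseline as day 0 these are days 28, 42, 56, 70 and 84. Applying ±5 days gives:

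| Visit | Window (days) | Gap before next window |
|---|---|---|
| 3 | 23-33 | 34-36 |
| 4 | 37-47 | 48-50 |
| 5 | 51-61 | 62-64 |
| 6 | 65-75 | 76-78 |
| 7 | 79-89 | none |

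A participant who comes for visit 3 on day 34 is a discontinuation, although the visit 4 window opens three days later.

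**Step 2: share classed as discontinued.** Let q be the chance that a given visit falls outside its window, taken as independent across visits. Over five visits the share is 1 − (1 − q)^5. Over visits 3-5 alone, nominally before weeks 9-12, it is 1 − (1 − q)^3.

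| Assumed q | Visits 3-5 | All five visits | Of 118 |
|---|---|---|---|
| 1% | 3.0% | 1 − 0.99^5 = 4.9% | about 6 |
| 2% | 5.9% | 1 − 0.98^5 = 9.6% | about 11 |
| 5% | 14.3% | 1 − 0.95^5 = 22.6% | about 27 |

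If lateness clusters in the same people, the share is smaller. In the extreme where the same participants miss every window, it is only q itself.

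**Step 3: direction of any bias.** Suppose there is no treatment effect, true abstinence is 40% in both arms, lateness is unrelated to abstinence, and every window-based discontinuation becomes a failure. With q = 2% under D-STOP and 5% under control:

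- D-STOP: 0.40 × 0.98^5 = 0.362
- Control: 0.40 × 0.95^5 = 0.310
- Odds ratio: (0.362/0.638) ÷ (0.310/0.690) ≈ 1.26

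With the two miss rates exchanged, the odds ratio is about 0.79. The mechanism can favour either arm.

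**Step 4: the sections side by side.** Take a participant admitted to hospital over a visit window. Design says this is not a withdrawal. Participants says that not attending in the window is discontinuation. The article does not say which prevails. Admission without a missed window raises no conflict.

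**The case against.** The strongest reply is that the article nowhere says that data collection ends or that late results are excluded. The failure rule is triggered by missing abstinence status, not by the label of discontinuation, and follow-up after discontinuation is commonly left to the full protocol. This stands as a limit on the point: the loss of data is an inference from the ordinary meaning of the word. It does not rescue the sentence, which is printed as an unqualified rule and, followed as written, leads to that loss.

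Other parts of the reply also stand. Retention already requires all procedures, so a visit missed altogether fails it anyway, and the window rule adds only visits attended late. Admission is recorded as relapse-related and relapse in weeks 9-12 is a failure in any case, so for the primary endpoint the hospitalization conflict matters mainly earlier in the trial. The encouragement described under Procedures concerns app use below 35%, not attendance, so the article gives no basis for calling a punctuality difference likely.

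Three stronger readings are tempting, and the article does not support them:

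- **A breach of intention to treat.** A reader might infer one, but Data Analysis says: "Participants who discontinue the study prematurely (dropouts) will be included in the analysis in accordance with the intention-to-treat principle". The two rules coexist. The trouble is avoidable missingness scored as failure.
- **A need to re-anchor the primary period.** The endpoint heading reads "Abstinence Success Rate During the Previous 4 Weeks" while its text says weeks 9-12, so a reader might propose the 28 days ending at the actual visit 7. If that visit fell on day 79, the period would be days 52-79 and would take in days 52-56 of week 8, when Procedures treats relapse as not disqualifying. Mapping visits to analysis periods is also usual analysis-plan content. Moving the period now would change the endpoint after an interim look at the primary outcome in an open-label trial.
- **A stated loss of power.** Such a figure would rest on abstinence rates and miss rates that the article does not give, so none is offered as evidence.

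**Conclusion.** The point holds as a badly fixed rule. As written, a single out-of-window visit is a discontinuation. Read with the urine component of the endpoint and the missing-is-failure rule, it can make an abstinent participant a primary failure. It also lowers retention for visits attended late, and it conflicts with Design when a hospitalized participant misses a window.

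The size is unknown. The illustrative 5%, 10% and 23% rest on assumed per-visit miss rates of 1%, 2% and 5%, on independence between visits and, for the effect on the primary endpoint, on collection stopping at discontinuation. Any bias could go either way. This calls for an inexpensive correction. It does not show that the primary analysis is invalid.

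**What to change.** Replace the sentence in Participants with wording to this effect: a visit outside its window is a protocol deviation; the participant remains in the study; later visits, urine tests and abstinence records are still collected and used; study discontinuation means withdrawal of consent or loss to follow-up. In Data Analysis, state that the failure rule applies only when the weeks 9-12 outcome itself is missing. Reconcile Participants with Design so that a hospitalized participant who misses a window has one stated status. Leave the primary period as it is.

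The cost is an amendment to the wording and some out-of-window visits in the data, reported as deviations. With 65 of 118 enrolled by March 6, 2026, the change can still protect data from the 53 yet to enrol and from those still in follow-up. Outcomes already lost under the present rule cannot be recovered. Because an interim analysis has been done, the amendment should be dated and should rest on this reasoning, not on results by arm. The number discontinued so far for lateness alone, pooled over arms, would replace the assumed miss rates.
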